| Trial registration:          | This trial is registered in the ClinicalTrials.gov registry and in the Swiss National Clinical trial Portal (SNCTP via BASEC)
FOPH Registration number:                                                                                                                                                                                                                                                                                                                                                                                                                                                                                        |
| Study category and Rationale | 
OClin category A
 
 
- The interventions assessed are the PCR on saliva and the RDT on nasopharyngeal swab against the reference test, which is the PCR on nasopharyngeal swab. RDTs on nasopharyngeal swabs are CE approved and used according to the manufacturer's instructions.
 
 
OClin category C
 
 
- The intervention assessed is the RDT on saliva against the reference test, which is the PCR on nasopharyngeal swab. RDT is CE approved but its use diverges from the manufacturer's instruction.
 
 |
| Clinical Phase:              | 
Diagnostic assessment
 
 
- Compare the detection rates of PCR on saliva, RDT on nasopharyngeal swab, RDT on saliva against PCR on nasopharyngeal swabs
 
                                                                                                                                                                                                                                                                                                                                                                                                                                      |

**Background and  
Rationale:**

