| 
Procedures:
 | 
Patients fulfilling inclusion and exclusion criteria will be recruited consecutively from the two testing sites of Unisanté (Bugnon 44 et Flon) and two testing site in town (Centre medical de la Source and Vidy-Med). After confirmation of inclusion and exclusion criteria (except for anticoagulation that will be asked later), patients will be asked whether they would be willing to provide two saliva samples and one nasopharyngeal swab in addition to that provided for routine testing. After written informed consent, patients will be asked to perform swabbing of the gingiva-buccal fold two times under professional supervision, once for sending to the laboratory to perform PCR, and once for performing the RDT onsite according to the below procedure. They will be taken two nasopharyngeal swabs, one for RDT and one for PCR.
 
The RDTs will be performed and results read according to the manufacturer information (see below).
 
The saliva and nasopharyngeal samples will be handled according to the procedures usually used for nasopharyngeal swabs. Samples will be forwarded to the Institute of Microbiology where they will be analysed by PCR according to the standard procedure (Corman et al 2020, Greub et al 2016, Pillonel 2020).
 
The patient will be considered as positive for SARS-CoV-2 if any of the PCR results or the RDT result on nasopharynx is positive. Indeed, the specificity of these three tests have been shown to be close to 100%. Moreover, in the presence of a suboptimal standard test (PCR on nasopharyngeal swab), it is possible to have higher or differential detection rate with the new tests. The result of the RDT on nasopharynx will be given on the spot because this test has now been validated in a clinical trial (https://www.medrxiv.org/content/10.1101/2020.10.01.20203836v1). The provision of an immediate response may decrease the refusal rate. Since the RDTs are less sensitive than PCR, we will inform patients who receive a negative RDT result that they have to wait for confirmation by PCR analysis before lifting isolation measures. PCR results will be forwarded to the patients using routine channels, the final result being negative if the two PCR and the RDT on nasopharynx are negative, or positive if any of these three tests are positive.
 
Because of problems in RDT availability and need for Swissmedic approval for the Oclin C component, we may start step by step:
 
 
1) PCR on saliva and nasopharyngeal swab
 
2) When RDT are available: PCR on saliva and nasopharyngeal swab + RDT on nasopharyngeal swab.
 
3) When RDT available and Swissmedic approval granted, all four components, namely PCR on saliva and nasopharyngeal swabs, RDT on saliva and nasopharyngeal swab.
 
 |

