| 
Intervention:
 | 
In spite of the difficulty to purchase antigen RDT, we were able to receive tests from three different brands that are all CE approved. In order to test the three different brands, and therefore have stronger generalization ability, we will rotate RDT brand use after 33 patients recruited. We started with the RDT from Roche (Standard Q COVID-19) (https://www.roche.com/media/releases/med-cor-2020-09-01b.htm), and then switch to RDTs from Abbott (Panbio COVID-19 Ag) (https://www.globalpointofcare.abbott/en/product-details/panbio-covid-19-ag-antigen-test.html) and then to those from AAZ-LMB (COVID-VIRO) (http://www.covid19aaz.com/). After 99 patients, we will start the cycle again and so on.
 
Saliva sample collections will be performed following the guidance published in Ott et al (2020) and Kojima et al (2020). Instead of collecting only saliva in a tube, the patient will perform him/herself a swab of the gingiva-buccal fold, under the supervision of a healthcare worker. A pilot test is ongoing at Unisanté to ensure appropriateness of swab type and procedure. The results of the first 10 positive patients done as a pilot show perfect concordance between PCR results on saliva and nasopharyngeal samples, with 1-3 log viral load less in saliva. Now that we got the RDT, we will follow the pilot on a few samples for RDT analysis on saliva.
 
No coughing or sniffing prior to sample collection is required. Ideally, water should be avoided 10 minutes prior to collection. Other drinks, food, and nasal sprays should be avoided 20 minutes before sample collection.
 
The health care worker must wear a personal protection equipment (at minimum, mask and gloves) prior to contact with the patient. The patient must clean his/her hands using alcohol-based sanitizer or soap and water (no fragrances).
 
The health care worker should verify all collection material labelling (at minimum, patient name/identifier and date and time of collection) with the patient. While preparing collection materials, he/she directs the patient to begin pooling saliva in his/her mouth.
 
If the RDT are available and Swissmedic granted, the following sampling procedure will be performed:
 
 
1) A first swab will be done on saliva by the patient using the 4 zones (gingiva-buccal fold left and right, tongue and palate) for 30 seconds to perform PCR (see video from 1:14 https://coronavirus.delaware.gov/drive-thru-testing-instructions-for-curative-test-english/).
 
2) The second swab will be on saliva collection. The health care worker will open the RDT kit, give the swab to the patient that will pass it for 30 seconds in the 4 zones of the gingiva-buccal fold. The health care worker will perform immediately the RDTs according to the manufacturer instruction as above, e.g (Standard Q COVID-19) (Roche/SD Biosensor : https://www.youtube.com/watch?v=mBdaOHJWxI4).
 
3) The third swab will be done on nasopharyngeal fluid by the health worker to perform PCR (reference test).
 
4) The fourth swab will be done on nasopharyngeal fluid by the health worker to perform the RDT. He will perform immediately the RDTs according to the manufacturer instruction.
 
 |

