|                                   | 
Should the patient refuse the second nasopharyngeal swab, the three other swabs will still be analysed and used for evaluation of detection rate.
 
Following collection, the patient should again clean his/her hands using alcohol-based sanitizer or soap and water. The health care worker will register the samples collection, and place the samples in a secondary container or a biohazard bag with a biohazard label.
 
The health worker will organize the transfer samples at room temperature to the laboratory for sample processing. The virus RNA in saliva remains stable at room temperature for 3-5 days.
 
The health care worker will wait for 15-30 min., read the result, take a picture of the RDT cassette with the tablet, and then transcribe the result in the Redcap database with the tablet. He/she will then inform the patients that has been waiting for the result in a dedicated waiting room.
 
If the RDT are not available, the following sampling procedure will be performed:
 
 
1) A first swab will be done on saliva by the patient using the 4 zones (gingiva-buccal fold left and right, tongue and palate) for 30 seconds to perform PCR (see video from 1:14 https://coronavirus.delaware.gov/drive-thru-testing-instructions-for-curative-test-english/).
 
2) The second swab will be on nasopharyngeal fluid by the health worker to perform PCR (reference test).
 
 
If the RDT are available, but Swissmedic submission not yet approved, the following sampling procedure will be performed:
 
 
1) A first swab will be done on saliva by the patient using the 4 zones (gingiva-buccal fold left and right, tongue and palate) for 30 seconds to perform PCR (see video from 1:14 https://coronavirus.delaware.gov/drive-thru-testing-instructions-for-curative-test-english/).
 
2) The second swab will be done on nasopharyngeal fluid by the health worker to perform PCR (reference test).
 
3) The third swab will be done on nasopharyngeal fluid by the health worker to perform the RDT. He will perform immediately the RDTs according to the manufacturer instruction.
 
 
Should the swab included in the RDT kit proves to be inappropriate for saliva collection (too small and therefore insufficient quantity of saliva, which leads to very low detection rate), a thicker swab will be tested. This will be piloted on few known positive samples by nasopharyngeal PCR, as we did in the pilot study for saliva collection for PCR analysis.
 |

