| Colonne1                                    | PANBIOTM COVID-19 Ag                                                                                                                                                                                    | BINAXNOWTM COVID-19 Ag CARD                                                                                             | LumiraDx SARS-CoV-2 Ag Test                                                                                                                                                                                 | Sofia SARS Antigen FIA                                                                                                                                                      | STANDARD Q COVID-19 Ag                                                                        | (2019-nCoV) Antigen Rapid Test Kit                                                                                                                                                                                                            |
|---------------------------------------------|---------------------------------------------------------------------------------------------------------------------------------------------------------------------------------------------------------|-------------------------------------------------------------------------------------------------------------------------|-------------------------------------------------------------------------------------------------------------------------------------------------------------------------------------------------------------|-----------------------------------------------------------------------------------------------------------------------------------------------------------------------------|-----------------------------------------------------------------------------------------------|-----------------------------------------------------------------------------------------------------------------------------------------------------------------------------------------------------------------------------------------------|

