| Durée de possibilité de lecture du résultat | 15 - 20 min                                                                                                                                                                                             | 15 min                                                                                                                  | 15 min                                                                                                                                                                                                      | 15 min                                                                                                                                                                      | 15 - 30 min                                                                                   | 10 min                                                                                                                                                                                                                                        |
| Nécessité lecteur optique (ou autre)        | non                                                                                                                                                                                                     | non, mais QR code et application pour le téléphone                                                                      | oui                                                                                                                                                                                                         | oui                                                                                                                                                                         | non                                                                                           | oui                                                                                                                                                                                                                                           |

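### One 15-30 minute reading window covers all three RDT brands, but the protocol's own Appendix 2 lists 15-20 minutes for Panbio, which is used in about a third of the rotation

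*Protocol*

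**What the plan says.** The operative instruction is in the Protocol synopsis, Intervention: "The health care worker will wait for 15-30 min., read the result, take a picture of the RDT cassette with the tablet". It names no brand and is the only reading time in the procedures.

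The same row describes three brands used in turn: "we will rotate RDT brand use after 33 patients recruited". Standard Q comes first, "and then switch to RDTs from Abbott (Panbio COVID-19 Ag"), and COVID-VIRO is third. "After 99 patients, we will start the cycle again and so on".

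Appendix 2 tabulates candidate antigen tests. Its first product column is "PANBIOTM COVID-19 Ag", and the row on how long a result stays readable begins "Durée de possibilité de lecture du résultat | 15 - 20 min". In the same row the Standard Q column shows 15-30 minutes. COVID-VIRO has no column.

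Two other rows of the synopsis commit the trial to the manufacturers' directions. Procedures: "The RDTs will be performed and results read according to the manufacturer information (see below"). Study category and Rationale, in the paragraph that places the nasopharyngeal RDT in category A: "RDTs on nasopharyngeal swabs are CE approved and used according to the manufacturer's instructions".

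**The concern.** The single window equals the Appendix 2 entry for Standard Q, the brand the trial started with. For Panbio it runs past the window that the protocol itself lists. Staff following the procedure to the letter can thus depart from what the synopsis says about manufacturer instructions.

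The readings matter for four reasons.

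- RDT positivity is primary outcome data (section 3.3.1).
- A positive nasopharyngeal RDT makes the patient positive whatever the PCR results show (synopsis, Procedures; section 2.6). It also enters the combined comparator against which the other methods are set (section 3.3.1). A non-standard reading can therefore touch both a test's own rate and the yardstick.
- The interim rule in section 3.3.2 can stop an RDT arm or switch the RDT type on the observed detection share after 200 patients.
- The variables listed in sections 5.1.1 and 5.2.1 include RDT results but neither brand nor reading time. On those lists alone, late readings could not be picked out afterwards. The cassette photograph may show the brand, but nothing says that elapsed time is captured.

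**Working it through.** **1. The windows side by side**

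| Brand (order in rotation) | Window in procedure | Window in Appendix 2 | Excess allowed |
|---|---|---|---|
| Standard Q (1st) | 15-30 min | 15-30 min | 0 min |
| Panbio (2nd) | 15-30 min | 15-20 min | 30 - 20 = 10 min |
| COVID-VIRO (3rd) | 15-30 min | not listed | cannot be checked |

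The lower limits agree. The conflict lies only in the upper limit for Panbio.

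**2. The protocol's cycle length**

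3 brands x 33 patients = 99, as stated. Panbio's share of a full cycle is 33/99 = 33.3%.

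**3. Number of Panbio patients at the planned size**

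Inputs: 1250 patients (section 3.2), one rotation across the study, every patient receiving RDTs.

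- 1250 = 12 x 99 + 62, so there are 12 full cycles and 62 further patients.
- Full cycles: 12 x 33 = 396 patients per brand.
- Remaining 62: 33 on Standard Q, then 29 on Panbio.
- Totals: Standard Q 429, Panbio 425, COVID-VIRO 396 (sum 1250).
- Panbio share: 425/1250 = 34.0%.
- With both a saliva and a nasopharyngeal RDT in each patient: 2 x 425 = 850 of 2500 cassettes.

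At the interim look after 200 patients, the same count gives 66 Panbio patients (33%).

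**4. From exposed to read late**

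Let f be the fraction of Panbio readings made after 20 minutes. The share of all RDTs outside the listed window is f x 425/1250. The protocol gives no value for f, so the whole range is shown.

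| f (assumed) | Patients | Share of all RDTs |
|---|---|---|
| 0 | 0 | 0% |
| 1/3 | 142 | 11% |
| 2/3 | 283 | 23% |
| 1 | 425 | 34% |

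The 2/3 row is what evenly spread reading times would give: (30 - 20)/(30 - 15) = 10/15.

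**5. What cannot be computed**

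The document gives no performance data for readings after 20 minutes, so neither the direction nor the size of any change in positivity can be derived.

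**The case against.** The best defence is that the passages can be followed together. The Panbio window lies wholly inside 15-30 minutes, so a worker who reads Panbio between 15 and 20 minutes complies with everything. The synopsis tells staff to perform both RDTs as the manufacturer directs and gives a link for each brand. This stands in part: the instruction permits late reading but does not direct it. It does not remove the conflict, because the one explicit time that staff are given is wider than the listed one for Panbio.

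Second, Appendix 2 is not a kit insert. The Background calls it an unpublished summary table and cites it for sensitivity. It covers six products, four of them outside the rotation. It also lists Panbio under a US emergency authorisation only, whereas the synopsis says all three brands are CE approved. This stands: the document shows a mismatch with its own secondary table, and whether the kit instruction itself would be breached cannot be seen here.

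Third, a reader might infer that a third of RDTs will be read late. The document does not support that. One third is the ceiling, reached only if every Panbio cassette is read after 20 minutes.

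Fourth, a reader might take the point to undermine the category A basis for all RDTs. It cannot: saliva RDT is already in category C because its use departs from the manufacturer's directions. Only nasopharyngeal RDTs are affected.

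Fifth, COVID-VIRO's absence from Appendix 2 might be read as a further contradiction. It is not; its window simply cannot be checked.

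Finally, time stamps and brand fields are often left to the case report form. Their absence from the data lists is not an error in itself. They belong in the remedy because they make late readings identifiable.

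**Conclusion.** The inconsistency is real and should be corrected, though its consequences are bounded and partly unknown. The procedure allows Panbio to be read up to 10 minutes beyond the window in the protocol's own table, while two rows of the synopsis say that manufacturer directions are followed.

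The exposed share is 33.3% per cycle and 34.0% (425 of 1250 patients) at the planned size. The share actually read outside the listed window could be anything from 0% to 34%.

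The counts assume that all 1250 patients enter one rotation and receive RDTs. PCR-only patients in the first step, a missing saliva RDT before Swissmedic approval, refusal of the second nasopharyngeal swab, or an arm stopped or switched at the interim would change the numbers. While the three-brand rotation runs, Panbio's share of RDTs would stay near one third.

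It would go too far to say that the detection rates are biased. No effect on positivity is shown, and section 3.3.1 plans no comparison between brands. The case for acting is that these are primary outcome readings, that a nasopharyngeal RDT positive counts on its own, and that the correction is nearly free. Which window is right for any brand is not decided here.

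**What to change.** Reconcile the synopsis rows on Study category, Procedures and Intervention with Appendix 2. Replace the single reading time with a reference to each brand's own window, taken from its kit instructions, and cover COVID-VIRO as well. If the kit instructions show that an Appendix 2 entry is wrong, correct the table instead of leaving the two in conflict.

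Add RDT brand and reading time (with test start, so that elapsed time is known) to the data lists in sections 5.1.1 and 5.2.1 and to REDCap. Out-of-window readings can then be identified and, if wanted, examined in a sensitivity analysis.

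The cost is one procedural line and a few data fields on a tablet form that staff already complete when they photograph the cassette. It needs no extra samples and no change to the sample size.

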## 2. ETHICAL AND REGULATORY ASPECTS

Before the study will be conducted, the protocol, the proposed patient information and consent testimony as well as other study-specific documents shall be submitted to the CER-VD, the properly constituted Competent Ethics Committee (CEC) in agreement with local legal requirements, for formal approval. Any amendment to the protocol will be approved (if legally required) by these institutions.

The decision of the CER-VD concerning the conduct of the study will be made in writing to the Principal investigator before commencement of this study. The clinical study for the PCR on saliva and nasopharyngeal as well as the RDT on nasopharyngeal can begin once approval from the CER-VD has been received.

Swissmedic approval will be asked for the conducting the RDT on the saliva 'arm'. The latter will only start after Swissmedic approval. Any additional requirements imposed by the authorities shall be implemented.

